### Outcome variables

A) Main effectiveness endpoint

Duration and severity of symptoms. Patients will complete a validated symptom questionnaire daily [see Additional file 2] [16].

B) Secondary effectiveness endpoints

The following variables will be assessed:

Use of antibiotics: patients will be asked about antibiotic use in their visit at 30 days and this will be crosschecked with the corresponding pharmacy units in the sanitary areas.

Satisfaction with the strategy (questionnaire with a Likert scale to patients).

Belief in the effectiveness of antibiotics (questionnaire with a Likert scale to patients and health professionals).

Perception about safety and effectiveness (questionnaire with a Likert scale to health professionals).

C) Safety endpoints

Complications related to the infections will be registered during the first 30 days after randomization. These complications will be prospectively recorded by the physicians by means of a standardized questionnaire and will be reported in a maximum of 48 hours to the study clinical coordinator. This researcher will report to the Safety and Data Monitoring Committee, whose aim is to assess the safety of the evaluated strategies. The Clinical Event Allocation Committee - blinded to treatment allocation - will assess the primary outcomes. The decisions of the Assessment Committee will be used in all the statistical analyses of the primary outcome. This Committee will meet quarterly.

### Enrollment

Enrollment will be carried out competitively at the participating physicians’ clinics and is expected to take one year. The study will be carried out in five Spanish Autonomous Communities (Catalonia, Galicia, Basque Country, Navarre and Madrid).

### Data collection

#### Initial visit

Baseline data will be collected in the clinic by the physician or with the help of the nursing staff. To standardize data collection, participants will be trained by the coordinating center. Patients will receive information about the study and, if they are interested in participating, an informed consent to read and sign will be handed to them. A maximum length of 10–15 minutes is expected for the interview and the introduction of the data.

After the randomization, information on the strategy to which they have been allocated will be given to the participants, and they will be informed on the appropriate measures to take in case of worsening or no improvement. Besides, they will be given a diary with a validated questionnaire of symptoms for each condition [16] which they should complete while symptoms related to the respiratory condition are present [see Additional file 2]. The degree of satisfaction or concern with different aspects of the therapy will also be recorded in this diary.

#### Follow-up

Patients will be interviewed by telephone after 48 hours of their inclusion in the study. Monitoring calls are also planned at day 7, 15 and 22 if symptoms are still reported by the patient on the calls. After 30 days, patients will visit their physician and then will submit the completed diary. We will also include a one year follow-up.

All the study data will be entered in an electronic platform (http://www.grupopreada.com).

### Data analysis

In order to ensure their similarities, a baseline comparison of the treatment groups will be performed. If any clinically relevant differences are found, a multivariate analysis will also be performed to ensure the absence of biases resulting from them. Differences will be deemed significant if p < 0.05. The SPSS software version 21.0 will be used for the calculations.

The comparisons among the treatment groups will be as follows: The differences for categorical variables will be described using contingency tables (and the corresponding percentages); inferencing will be made by means of an exact Fisher test or Chi-square test. The Kruskall-Wallis test will be used for ordinal or quantitative variables with heteroscedasticity or abnormality issues. In case of significance, the decision on the groups will be based on the 2 × 2 Mann–Whitney test; no corrections will be applied for multiple comparisons, calculated the means and the higher and lower values for each group. For quantitative variables, the analysis of variance (ANOVA) test will be used, resorting to post-hoc in case of significance, thus showing the means and the standard deviations for each group.

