### Randomization

Stratified by condition of interest (pharyngitis, rhinosinusitis, acute bronchitis, and exacerbations of chronic obstructive pulmonary disease). Centralized using a Web-based platform.

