### Study population and total number of patients

The sample size calculated is 600 patients. This is an estimate based on an average duration of 12 days (s.d. 6) for the main symptoms [16]. Considering a reduction of two days in the duration of the symptoms as a clinically relevant outcome, with a bilateral approximation, a sample of 600 patients will be able to detect this difference with an alpha error of 5% and a power of 80% (beta = 0.2). This estimate was calculated considering lower respiratory tract infections only. The project aims to be much broader (and therefore pragmatic, with an increase in the external validity at the conceptual phase), for this reason an exhaustive search will be carried out for all the conditions initially expected to be included (pharyngitis, rhinosinusitis, acute bronchitis, acute exacerbation of chronic bronchitis). The aim of this search is to obtain average values of the main endpoints defined in this project and to allow for standardization, and accordingly, a comparison (the variability that can be derived from the data obtained for the calculation has reached 50%, which indicates a high dispersion). It seems unlikely that the remaining conditions exceed that value, and generally, they will even tend to be lower. This allows avoiding the estimation of losses in the required total number of patients.

The patients will be equally distributed among the four evaluation groups to maximize power in the comparison. In addition, the four groups will be stratified in terms of the included conditions. Besides, focusing on the three groups except for the immediate antibiotic therapy, the 450 patients distributed in the three arms would allow to detect a difference of at least 13% in antibiotic use with the same indicated power (assuming that the figures for antibiotic use in the two delayed strategies are very similar: delayed strategy group 27% versus 14% in the group with no antibiotic therapy). Finally, in the comparison of four strategies for the variable *antibiotic use*, the study will have a 100% for antibiotic use as an outcome, since the percentage of antibiotic use in the antibiotic therapy arm is likely to exceed 90%. For the calculations we used Sample Power Release 2.0 software.

Criteria for withdrawals and expected analysis of withdrawals and dropouts:

•Serious adverse event

•Unsatisfactory therapeutic effect

•Patient clinical conditions prevent compliance with the protocol

•Protocol violation

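### Randomisation is stratified by condition, but the stated tests carry no condition term and adjustment waits on observed baseline differences, so precision may be lost

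*Protocol article*

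**What the plan says.** Under Randomization, allocation is "Stratified by condition of interest (pharyngitis, rhinosinusitis, acute bronchitis, and exacerbations of chronic obstructive pulmonary disease"). The sample-size section (Study population and total number of patients) repeats this: "the four groups will be stratified in terms of the included conditions".

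The Data analysis section then names the between-group tests:

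- Categorical outcomes: "inferencing will be made by means of an exact Fisher test or Chi-square test".
- Ordinal or non-normal outcomes: "The Kruskall-Wallis test will be used for ordinal or quantitative variables with heteroscedasticity or abnormality issues". If that test is significant, "the decision on the groups will be based on the 2 × 2 Mann–Whitney test; no corrections will be applied for multiple comparisons".
- Other quantitative outcomes: "For quantitative variables, the analysis of variance (ANOVA) test will be used, resorting to post-hoc in case of significance".

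None of these is described as stratified by condition or as containing a condition factor. The one provision for adjustment follows a baseline comparison of the arms: "If any clinically relevant differences are found, a multivariate analysis will also be performed to ensure the absence of biases resulting from them". The covariates, the threshold for a relevant difference, and which result prevails if the two analyses disagree are not stated.

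**The concern.** Stratifying the randomisation treats condition as a factor worth controlling. The benefit reaches the standard error and the p-value only if the analysis also uses condition. Otherwise the between-condition variation that the design has balanced out of the arm comparison stays in the error term. The standard error is then too large and the test rejects less often than its nominal 5%.

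The adjustment rule does not repair this. It responds to observed imbalance, and condition is the one factor that the design keeps balanced, so it is the factor least likely to trigger the rule. Any other covariate would enter only after the baseline data have been seen.

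At stake is the precision of the comparison of symptom duration, the main endpoint and the one on which the trial is sized. The sample-size section makes no allowance for losses, so spare precision is worth keeping.

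**Working it through.** **Inputs from the sample-size section.** Total 600 in four equal arms, so 150 per arm; mean duration 12 days, SD 6; relevant difference 2 days; two-sided 5%; power 80%. The section says that the estimate considered lower respiratory tract infections only.

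**Assumed input.** R², the share of outcome variance explained by condition. The documents give no outcome by condition, so R² is varied from 0 to 0.25. Strata are taken as well balanced across arms.

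**The plan's own figure.** For one pairwise comparison, n per arm = 2 × (1.960 + 0.842)² × 6² / 2² = 141.3, so 142 per arm and 568 in total. Allowing for the Mann-Whitney test (relative efficiency 0.955), 142 / 0.955 = 148.7, so 149 per arm and 596 in total. With 150 per arm, the standard error is 6 × √(2/150) = 0.693 and power is Φ(2/0.693 − 1.960) = Φ(0.927) = 82.3%. The figure of 600 is adequate for its own inputs and is not in dispute.

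**Case A: SD 6 is the pooled SD over all conditions.** The unstratified test uses SE_total = 0.693. The true standard error under stratified allocation is SE_within = 0.693 × √(1 − R²).

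- True size, unstratified = 2 × [1 − Φ(1.960 / √(1 − R²))]
- Power, unstratified = Φ((2 − 1.960 × SE_total) / SE_within)
- Power with condition = Φ(2 / SE_within − 1.960)

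| R² | SE_within | True size, unstratified | Power, unstratified | Power with condition |
|---|---|---|---|---|
| 0 | 0.693 | 5.0% | 82.3% | 82.3% |
| 0.05 | 0.675 | 4.4% | 82.9% | 84.2% |
| 0.10 | 0.657 | 3.9% | 83.6% | 86.1% |
| 0.20 | 0.620 | 2.8% | 85.0% | 89.8% |
| 0.25 | 0.600 | 2.4% | 85.8% | 91.5% |

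Simulation (two arms of 150, four balanced strata, 10,000 runs per setting) agrees. The unadjusted test had size 0.036-0.042 at R² = 0.10 and 0.028 at R² = 0.20. With condition in the model the size was 0.046-0.055.

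**Case B: SD 6 is the within-condition SD.** This is possible because the value comes from lower respiratory infections only; it assumes the same within-condition SD for the other conditions. The pooled SD is then 6 / √(1 − R²), SE_within stays at 0.693, and SE_total = 0.693 / √(1 − R²). The power formulas are unchanged.

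| R² | Pooled SD | SE_total | Power, unstratified | Power with condition |
|---|---|---|---|---|
| 0 | 6.00 | 0.693 | 82.3% | 82.3% |
| 0.05 | 6.16 | 0.711 | 80.9% | 82.3% |
| 0.10 | 6.32 | 0.730 | 79.4% | 82.3% |
| 0.20 | 6.71 | 0.775 | 75.7% | 82.3% |
| 0.25 | 6.93 | 0.800 | 73.4% | 82.3% |

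Unstratified power crosses 80% between R² = 0.05 and 0.10. The size of the unstratified test is the same as in case A.

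**The case against.** **The text is a short journal article, and silence on a model term is not a statement that it is absent.** This has some force for ANOVA, which can hold a condition factor. It has less for Kruskal-Wallis, Mann-Whitney, chi-square and Fisher, which have no stratum in their usual form. The article also goes beyond silence: it states when adjustment will happen and ties it to observed differences.

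**A reader might infer an inflated false-positive rate.** The documents do not support that. Ignoring balanced strata moves the error rate down. The imbalance-triggered model could move it either way, but that depends on how the result is used. Simulation with an assumed covariate correlation of 0.5 and R² = 0 gave 0.034-0.036 if the adjusted result replaced the unadjusted one, and 0.048-0.058 if either could count. The plan states neither use. It says that the model is performed *also*, which reads as an addition, with precedence left open.

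**A reader might infer that severity scores from different questionnaires are compared on one scale.** Patients do receive condition-specific instruments ("they will be given a diary with a validated questionnaire of symptoms for each condition"), but pooling of raw scores is not stated. The sample-size section mentions standardisation to allow a comparison, and the questionnaires are in an additional file that is not shown. Nor does the Data analysis section mention confidence intervals, so their width is not a fault of the stated plan.

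**Nothing anchors R².** This stands. No duration by condition is given, and the sample-size section speaks only of dispersion, which it expects to be no larger in the other conditions. At R² = 0 nothing is lost. In case A, unstratified power also stays above the 80% target throughout.

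**The figures describe one two-arm test.** This stands too. The plan is a four-group test with pairwise tests after significance, so the figures show direction and rough scale, not the operating characteristics of the full procedure.

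**Conclusion.** The point holds as a matter of efficiency. The design stratifies by condition; the stated tests do not use it, and the stated adjustment rule is unlikely to bring it in. If outcomes differ by condition, the consequence is a conservative test and lost precision, without bias in differences of means.

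The size of the loss cannot be fixed from the documents. For a single comparison of two arms of 150 with R² between 0 and 0.25:

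- With SD 6 as the pooled value, the cost is between nothing and 5.7 power points (91.5% − 85.8%).
- With SD 6 as the within-condition value, the cost is up to 8.9 points (82.3% − 73.4%), and unstratified power misses the stated 80% from an R² of roughly 10% upward.

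The analysis should be changed, but the validity of the trial does not depend on it.

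**What to change.** In the Data analysis section, state that every between-group analysis includes condition, whether or not baseline differs:

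- a condition factor in the ANOVA or linear model, including its pairwise comparisons;
- stratified rank tests (van Elteren) in place of unstratified rank comparisons;
- Mantel-Haenszel, or logistic regression with condition, for antibiotic use.

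Label the imbalance-triggered multivariate model as a sensitivity analysis only. Any other covariate wanted in the main analysis should be named in advance and used regardless of observed balance.

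The cost is a change of analysis wording. Condition is already recorded for the stratified randomisation, so no new data, patients or visits are needed.

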#### Ethical issues

The protocol was approved by the Ethics Committee of Clinical Investigation *IDIAP Jordi Gol i Gurina* and by the Ethical Committees of Clinical Research in the corresponding health care areas and Spanish Agency of Medicines and Health Products. Each patient should give their written consent to participate in the study after being informed in intelligible language for him on the nature, scope and possible consequences of the trial. After consent is submitted, the patients will be randomized.

Data confidentiality will be ensured at all times, as it is stated in the researcher’s commitment sheet, as well as the compliance with current legislation regarding the protection of personal data. The clinical trial will be insured by the health provider to which the different participating health centers belong.

#### Other considerations

This is a clinical trial based on the outpatient setting, and no monetary compensation is given to either patients or researchers. Sponsorship is only reserved for the purposes of organization and implementation of the trial.

## Discussion

The main issue addressed in our study is the effectiveness of the delayed antibiotic prescribing strategy in uncomplicated respiratory infections. To achieve this we will compare two delayed prescription strategies with immediate antibiotic prescribing and no prescription. Specifically, symptom duration and severity, patient satisfaction, belief in the effectiveness of antibiotics and antibiotic use in the different strategies will be assessed.

There are two main types delayed strategies. One where patients are asked to return to the reception of the primary health center in order to collect the prescription, and another one in which the prescription is handed in the initial visit. The rationale for the former being that asking the patient to return could further reduce subsequent use of antibiotics [13,23].

Delayed antibiotic prescribing has been used not only for respiratory tract infections but also for other types of diseases [18,19]. So far, these studies have shown [20], that these strategies reduce antibiotic use. As to patients’ satisfaction, a qualitative study in patients with conjunctivitis showed that this strategy is usually well received [18] and another in women with urinary tract infections [19] showed positive perceptions too. In one of them there is the paradox that those patients who know that their condition is mild but still feel that they need them, given their strong belief in the need of a therapy [18]. As to the physicians [21], they highlight that these strategies can be of help in cases of uncertainty, since patients can gain fast access to antibiotics and in addition, the strategy reassures them too.

In our study the two delayed strategies will be compared with other alternatives and with each other. We also wish to find out whether they are effective reducing the number of new visits. Antibiotic prescribing in the clinic leads to a vicious circle in which the patient perceives that an antibiotic treatment is necessary, it increases the number of new visits for the same reason and increases the chance of requesting a new antibiotic in similar episodes in the future [11]. Consequently, we will evaluate differences among the delayed prescribing strategies in terms of the number of new visits and the immediate antibiotic prescribing strategy.

Delayed strategies are also criticized for an increased possibility of complications. In order to avoid them, it is crucial to bear in mind that these are not used in the case of patients presenting with supposedly bacterial infections, and reserved in the event of reasonable uncertainty. They should not be used in critically ill patients or those meeting criteria for admission [24].

Two systematic reviews have studied the use of delayed strategies and both have showed significant advantages. One of them [23] showed that for most of the symptoms no significant differences in duration have been observed compared with immediate antibiotic prescribing. In a more recent systematic review Spurling et al showed that delayed prescription significantly reduces antibiotic consumption [20].

Further studies [25] conclude that delayed prescribing is an acceptable option, reflected in small differences in terms of the resolution of the symptoms, and a considerable reduction in antibiotic use and in the confidence in its effectiveness. The number of randomized patients is still scarce and the results for some of the outcome are non conclusive. Nevertheless, some institutions such as NICE start to recommend it as an initial strategy for self-limiting respiratory tract infections [26].

Our study has several strengths but also some limitations. For example, the open-label design of the trial could imply a placebo effect favoring antibiotics. This effect is minimized given the structured approach that physicians will apply to support and increase the confidence in each strategy. In previous studies this placebo effect has been minimal in favor of antibiotics or has not been recorded [11,25]. Another limitation in our study is the absence of a unique consensus definition for respiratory tract infections. Due to this, we will use the definitions used in the main published cohort studies [27].

One of the important strengths of our study is the inclusion of all the main respiratory tract infections, considering for the first time the exacerbations of mild to moderate COPD. Besides, it will be the first study to compare two delayed strategies directly. The pragmatic character of the study increases the external validity of the results and this is of special interest to our health system priorities.

The confirmation of our hypothesis will likely reassure physicians about the effectiveness and safety of these delayed strategies. This fact could facilitate their implementation in our country and, thus, help optimizing antibiotic prescribing. We believe that our results will likely help to change patients’ perception about the role and need of antibiotics.

The impact of our trial is likely to be important since the available evidence in this field is still limited, and new larger studies, adequately designed and conducted, are warranted to clarify the effectiveness of these strategies. Similarly, including most of the uncomplicated respiratory infections will increase the external validity of the results. Comparing, for the first time, two delayed strategies will provide information on the possible differences within this modality. These characteristics make this study innovative and relevant to this field.
